### Outcome Parameters

An overview of the outcome parameters related to the primary, secondary, and tertiary hypotheses is presented in Table 4. The raw data, processed data, and task parameters are described in detail next.

**Table 4 table4:** List of outcome parameters according to primary, secondary, and tertiary hypotheses.

Hypotheses	Outcome measures
Primary	Frontal knee angle RoM^a^ (°) Pelvic obliquity angle RoM (°) Frontal trunk angle RoM (°)
Secondary	HHS^b^ (sum) HOOS^c^ (sum) SF-12^d^ (sum) IPAQ-SF^e^ (sum) KOOS^f^ (sum)
Tertiary	3DMA^g^ kinematic parameters 3DMA kinetic parameters 3DMA spatiotemporal parameters

^a^RoM: range of motion.

^b^HHS: Harris Hip Score.

^c^HOOS: Hip Osteoarthritis Outcome Score.

^d^SF-12: 12-item Short Form Health Survey.

^e^IPAQ-SF: International Physical Activity Questionnaire –Short Form.

^f^KOOS: Knee Injury and Osteoarthritis Outcome Score.

^g^3DMA: three-dimensional movement analysis.

#### Raw Data

Raw data are defined as directly measured data before they have been processed. The raw 3D data file is a binary file that will contain the recorded marker positions of the individual cameras, and another binary file exists that will contain the analog input signals of the force plates.

#### Processed Data

Processed data are data that are constructed from raw data. The data from the individual cameras will be merged and the trajectories of the markers reconstructed. Next, the trajectories will be filtered and a label assigned to them. A biomechanical model will be constructed using the data from the marker trajectories and the force plates. This biomechanical model will provide the trajectories of joint angles, joint moments, joint powers, and ground reaction force. These trajectories, as well as the anthropometric data collected and the time points of gait events, will be stored in binary form in so-called c3d-files

#### Analyzed Data

The parameters related to locomotion tasks will be normalized to gait and stance phases. The stance phase will be defined between the heel-strike and toe-off of the observed leg. Cyclic tasks will be normalized to start, turn, and end events. The circuit task TuG will be split into sit-to-walk, straight walking, turn, and walk-to-sit. STS and STSr will be analyzed according to the literature using the lift-off event. The ADL task SQL will be spatially defined by start, turn, and end events. During the exploration of the database, new variables will be calculated and reported.

Kinematic data will be time-normalized from heel strike to heel strike, and kinetic data will be time-normalized from heel strike to toe-off. Individual participant data will be expressed as an average per condition. Time normalization, data processing, and parameter calculations will be conducted using self-developed scripts in MATLAB 2018a (Mathworks). The analyzed data will be stored as single cycles, averaged cycles, and single data at certain time points in a .mat file. With the help of a self-written MATLAB tool, these .mat files will be made searchable with arbitrary filter settings. All data can also be used in future analyses according to the latest scientific knowledge.

#### Activity-Monitoring Data

Activity-monitoring data collected for 2 days prior to surgery and at t_0_, t_1_, and t_2_ for 7 days will be stored as acceleration raw data and analyzed using the latest version of ActiLife software (ActiGraph LLC). Prior to parameter calculation, cutoffs of a minimum of 10 hours wear time a day, 3 valid weekdays, and 1 valid weekend day will be applied. Physical activity intensity will be categorized and daily step counts extracted [36].

#### Body Composition Data

Raw data of body composition measurements will be processed for the parameters body muscle mass, left and right leg muscle mass, and body fat rate.

#### Patient Characteristics

In addition to age, gender, and biometric characteristics, each patient’s additional information, such as therapy adherence and physical activity, will be obtained for a possible confounding effect on the results (Table 5).

**Table 5 table5:** List of patient characteristic parameters.

Characteristic	Measure
Biometric	Body height (m) Body mass (kg) Body fat mass (% body weight [BW]) Muscle mass (% BW) Left/right muscle mass (kg)
Personal	Age Gender Private health insurance Surgeon Therapy adherence (by category) Physical activity (by activity category and step counts)

### Statistical Analysis

Data will be inspected for outliers using boxplots. Shapiro-Wilk tests and additional graphical inspections of q-q plots will be applied to test for the normality assumption. Metric baseline characteristics will be indicated as means (SDs) and categorical baseline characteristics as frequencies (n, %). Unadjusted outcome scores will be reported as means (95% CIs). People from the same cluster tend to be more similar than those from different clusters, and the analysis must allow for this. A common enhancement is to apply a linear mixed effects model with the cluster specified as a random intercept. To model changes between baseline and follow-up, we will include baseline measurements as covariates. Following suggestions by Klar and Darlington [37], we will adjust for each participant’s baseline assessment and for the baseline cluster mean. Otherwise, no adjustments for covariates are foreseen. Treatment effects will be reported independently for follow-up t_1_ and follow-up t_2_, including unstandardized and standardized regression coefficients as effect estimates, standard errors, *t* statistics, and appropriate *P* values via the Satterthwaite degrees-of-freedom method. Between-cluster and residual variances will be reported for all outcomes. In the case of severe outliers or major violations of the normality assumption, logarithmic data transformation approaches will be explored. Outcome parameters on the ordinal scale will be analyzed descriptively and reported as medians with ranges. All descriptive statistics and corresponding numbers of subjects (n, %) will be reported, along with losses to follow-ups. Effect sizes will be calculated and reported accordingly (per protocol). In addition, the hypotheses will be analyzed according to the intention-to-treat principle (last value carried forward), providing a more conservative effect estimate [38] when missing observations introduce bias. The α value will be set to .05, and exact 2-sided *P* values will be reported. Hypotheses will be tested independently of each other. The 2-armed study design does not require post hoc tests, so no adjustment for familywise α error accumulation is needed.

Additionally, the agreement between the RTF prototype and the optoelectronic reference system will be analyzed. The spatial deviation of anatomical body key points from the reference system’s key points will be determined using the root mean square error (RMSE). The measured RoM for the angle between the trunk and the thigh, as well as the angle between the thigh and the shank, will be displayed and interpreted using the Bland-Altmann plot.

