**Methods:**

A clinical trial with a cluster-randomized, 2-arm, parallel-group design with an 8-week intervention phase and subsequent follow-ups at 3 and 6 months postsurgery will be conducted. Feedback during exercising will be provided through a blended-care program, combining a supervised group exercise program with a self-developed digital feedback system for home exercise. In total, 70 patients will be recruited for baseline. The primary outcome parameters will be the frontal knee range of motion, pelvic obliquity, and lateral trunk lean. Secondary outcomes will be the sum scores of patient-reported outcomes and relevant kinematic, kinetic, and spatiotemporal parameters.

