
### Study Goals

This pilot cluster-randomized, 2-arm, parallel-group controlled trial aims at enhancing the understanding of the effects of RTF on functional deficits such as knee valgus thrust, pelvic drop, and lateral trunk lean after THA. Biomechanical and patient-reported outcomes will be assessed prior to the intervention, as well as at 3- and 6-month follow-ups postsurgery.

The primary research question is whether blended-care digital RTF-supported home exercise (intervention group [IG]) leads to significant higher improvements in the control of the frontal knee range of motion (RoM), pelvic obliquity, and lateral trunk lean compared to blended-care exercise supported by written instructions (control group [CG]) as a comparator. The secondary aspect will focus on potential differences between groups concerning aspects of the quality of life, function, and physical activity. Tertiary functional outcomes between groups will be compared to quantify movement quality. Consequently, the underlying primary null hypotheses were prespecified as follows:

Improvements in the frontal knee RoM are equal between the IG and the CG.Improvements in pelvic obliquity are equal between the IG and the CG.Improvements in lateral trunk lean are equal between the IG and the CG.

In addition, the primary alternative hypotheses are as follows:

Improvements in the frontal knee RoM are not equal between the IG and the CG.Improvements in pelvic obliquity are not equal between the IG and the CG.Improvements in lateral trunk lean are not equal between the IG and the CG.

The 3 primary outcomes (frontal knee RoM, pelvic obliquity, and lateral trunk lean) will be tested in 3 independent hypotheses (each parameter will be tested independently of the others in 2 follow-ups).

Secondary hypotheses will be tested independently for differences between the IG and the CG in a series of metric patient-reported outcomes measures (PROMs): (1) the Harris Hip Score (HHS), (2) the Hip Osteoarthritis Outcome Score (HOOS), (3) the 12-item Short Form Health Survey (SF-12), (4) the International Physical Activity Questionnaire – Short Form (IPAQ-SF), and, if applicable, (5) the Knee Injury and Osteoarthritis Outcome Score (KOOS).

Tertiary hypotheses will be tested independently for differences between the IG and the CG in a series of metric movement analysis outcomes, including (1) kinematics, (2) kinetics, and (3) spatiotemporal results.

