### Sample Size Estimation and Study Population

As knowledge and studies concerning the effect of RTF on exercise following unilateral THA are missing, the sample size cannot be calculated based on given effect sizes. Therefore, the sample size for comparing 2 independent means was calculated using an estimated effect size (d) of 0.8. Assuming the planned 16 clusters with a cluster size of 3 participants each and an intracluster correlation of 0.05, a nominal sample size of 24 participants per group would give a power of 0.75 (α=.05). The effect size (d) of 0.8 and the intracluster correlation of 0.05 were estimated, and hence, the achieved power in this pilot cluster-randomized trial will be reported. The number of participants included in topic-specific studies range from 14 to 111 [5,11,14,25,26]. Considering a dropout of 30%, we will recruit 70 participants from the Orthopedic Hospital Speising, Vienna, Austria.

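### A two-arm design does not remove the multiplicity of six primary tests (three outcomes at two follow-ups), each at two-sided .05

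*Protocol article*

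**What the plan says.** The Abstract (Methods) lists three primary outcomes: "The primary outcome parameters will be the frontal knee range of motion, pelvic obliquity, and lateral trunk lean". Study Goals sets out one primary null hypothesis and one two-sided alternative for each, and adds that "each parameter will be tested independently of the others in 2 follow-ups".

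Statistical Analysis keeps the two visits apart: "Treatment effects will be reported independently for follow-up t_1_ and follow-up t_2", each with its own estimate and P value. It fixes the level: "The α value will be set to .05, and exact 2-sided *P* values will be reported". It then states "Hypotheses will be tested independently of each other" and closes with "The 2-armed study design does not require post hoc tests, so no adjustment for familywise α error accumulation is needed".

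The article names no main follow-up, no order of testing, no split of alpha and no rule on how many of the six results must be significant. Sample Size Estimation and Study Population plans for a single comparison of two means at α = .05.

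**The concern.** The closing sentence of Statistical Analysis draws a conclusion that its premise does not support. With two arms there is only one between-arm contrast, so pairwise post hoc tests are indeed unnecessary. Error accumulation over outcomes and visits is a separate matter, and here it comes from 3 outcomes × 2 follow-ups = 6 primary tests.

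This is an explicit statement, not a detail left to a fuller document. An analysis plan that did adjust would contradict it.

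At stake is how a positive primary result can be read. Study Goals poses a single primary question, feedback-supported versus written home exercise, that spans all three outcomes. No rule says which visit decides any of them. A single significant result among six would therefore carry much weaker evidence than the .05 level suggests.

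**Working it through.** **Inputs.** Level .05, two-sided (Statistical Analysis). Three primary outcomes, each tested at two follow-ups (Study Goals). Effect size 0.8, 16 clusters of 3, intracluster correlation 0.05, 24 per group, stated power 0.75 (Sample Size Estimation and Study Population). The document gives no correlation between outcomes or between visits, so those below are assumptions.

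**Step 1: reproduce the stated power.**
- Design effect = 1 + (3 − 1) × 0.05 = 1.10.
- Effective n per arm = 24 / 1.10 = 21.8.
- Expected z = 0.8 × √(21.8 / 2) = 2.642.
- Power = Φ(2.642 − 1.960) = 0.752.

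The stated 0.75 is reproduced, for one test at two-sided .05 by the normal formula.

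**Step 2: familywise error if the tests are independent.**
- Six tests, either direction: 1 − 0.95⁶ = 26.5%.
- Six tests, false results favouring feedback only: 1 − 0.975⁶ = 14.1% (single test: 2.5%).
- Three outcomes at one visit, either direction: 1 − 0.95³ = 14.3%.
- One outcome at two visits, either direction: 1 − 0.95² = 9.75%.

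**Step 3: familywise error if the tests are correlated.** Six z-statistics were simulated under the null, 1,000,000 draws per setting, with one common correlation between outcomes and one between visits.

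| Between outcomes | Between visits | Either direction | Favouring feedback |
|---|---|---|---|
| 0 | 0.5 | 24.8% | 13.0% |
| 0.5 | 0.7 | 20.3% | 10.2% |
| 0.7 | 0.7 | 17.7% | 8.8% |
| 0.5 | 0.9 | 17.2% | 8.6% |
| 0.7 | 0.9 | 15.0% | 7.5% |

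**Step 4: what adjustment costs in power.** At the strictest Holm step over three outcomes, .05 / 3 = .0167, the critical value is 2.394. Power is Φ(2.642 − 2.394) = 0.60 by the formula of step 1. At the strictest step over six tests, .05 / 6 = .0083, the critical value is 2.638 and power is 0.50.

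With t-distributions on 14 to 46 degrees of freedom, power at .0167 is 0.49 to 0.57. Those distributions give 0.69 to 0.73 at .05, so they start from a lower baseline than the stated 0.75.

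**The case against.** The strongest defence is that this is a pilot with three separately stated hypotheses. Effect size and intracluster correlation are acknowledged to be estimates, planned power is only 0.75, and leaving separate hypotheses unadjusted in a pilot can be defended. All six results are to be reported with exact P values, so readers would see them together. If each claim is confined to its own outcome, the error is 5% at one visit and 9.75% over two independent visits.

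Much of this stands. It means that alpha control is not the only acceptable answer. It does not rescue the sentence as printed, which gives the number of arms as the reason, not the pilot status. Nor does the text call the primary tests exploratory: it presents them as prespecified primary hypotheses.

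Two stronger readings should be resisted.
- A reader might infer that the chance of a false claim for feedback is 20% to 26%. That range counts false results in both directions and assumes no more than moderate correlation. Errors favouring feedback are about half as frequent, and strong correlation brings the two-sided figure down to about 15%.
- A reader might infer that the protocol lets any one significant result establish that feedback works. No such rule is written. The protocol simply does not say what would count as primary success.

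The patient-reported and remaining movement outcomes are already labelled secondary and tertiary, so no change is needed there.

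**Conclusion.** The point holds. The stated reason for not adjusting is wrong, and six primary tests at two-sided .05 are left with no rule linking them.

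The chance of at least one false significant primary result in either direction is 26.5% under independence. It is about 15% to 25% with assumed correlations of 0 to 0.7 between outcomes and 0.5 to 0.9 between visits. For false results favouring feedback the figure is about 7% to 14%, where the upper end is the independence value, against 2.5% for a single test.

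The exact size depends on correlations that the document does not give. Under every setting examined, the error is about three times the single-test level or more.

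**What to change.** Delete the two-arm justification. Then, by a documented amendment made before any outcome data are compared by arm:

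- name one follow-up as primary;
- control familywise error over the three outcomes there, with Holm or with a fixed sequence stated in advance;
- treat the other follow-up as supportive.

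If this can no longer be done credibly, either apply Holm over all six tests, or state that this is a pilot, that the six primary tests are unadjusted and exploratory, and that no single significant result will be claimed as confirmatory.

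**Cost.** The sample size and assessments do not change, but this is more than rewording. The trial started in January 2024, is registered and has ethics approval, so changing the primary testing rule needs a protocol amendment and a registry update.

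Holm over three outcomes lowers power at its strictest step from 0.75 to about 0.60 by the protocol's own formula; Holm over six lowers it to about 0.50. A fixed sequence costs no power for the first outcome, but later outcomes can be claimed only if the earlier ones succeed. The exploratory route costs no power but gives up any confirmatory claim.

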**Figure 2 figure2:**
[figure not shown]
System components of the prototype.

The recorded image data, which may potentially identify a person, will be solely used for key point recognition purposes and will not be stored in any form. The RTF prototype has no wireless local area network (LAN), and the existing LAN connection is covered by the housing. Therefore, an internet connection is excluded and access from outside is not possible. The complete data processing will be carried out locally on the prototype. The following data will be stored on the SD card of the prototype: test person ID, body height, training time, achieved exercise scores, number of repetitions of the exercises, and coordinates of the key points. The SD card is located inside the housing, making it difficult to access or remove. The data from the SD card will be analyzed only by the project team and will not be passed on to third parties.

The prototype is not certified as a medical device and was therefore submitted to the Austrian Federal Office for Safety in Health Care for a safety review after a successful ethics vote. Relevant individual parts have a Conformité Européene (CE) mark of conformity.

To compare the RTF prototype with the optoelectronic reference system Vicon Nexus, both systems will be synchronized both temporally and spatially. Temporal synchronization will be achieved through a time-to-live (TTL) signal sent from the prototype to the reference system. Spatial synchronization will be ensured by calibrating the prototype’s coordinate system to match the reference coordinate system. For assessing this agreement, testing participants from the IG will perform a single set of their home exercise program at t1 after performing the set of ADL tasks.

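### The device-agreement analysis compares angles only through range of motion, so the prototype's angle bias in degrees stays unquantified

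*Protocol article*

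**What the plan says.** The last paragraph of the Statistical Analysis section states that "the agreement between the RTF prototype and the optoelectronic reference system will be analyzed". It names two measures. The first is the deviation of the prototype's key points from the reference key points, summarised as an RMSE. The second concerns angles. Its variable is "The measured RoM for the angle between the trunk and the thigh, as well as the angle between the thigh and the shank", and the plan for these values is that they "will be displayed and interpreted using the Bland-Altmann plot". No other angle quantity is named.

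The section on agreement of the real-time feedback system describes the data. For this comparison "both systems will be synchronized both temporally and spatially". In time: "Temporal synchronization will be achieved through a time-to-live (TTL) signal sent from the prototype to the reference system". In space, the prototype is calibrated for its "coordinate system to match the reference coordinate system". Intervention-group participants perform one set of their home programme at t1, and the prototype stores key-point coordinates. The Processed Data section mentions filtering of the reference marker trajectories. No filter is stated for the prototype signal.

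**The concern.** An agreement analysis should let a reader say how far, and in which direction, the new device departs from the reference. RoM is a difference between two extremes of the same series. Subtracting removes any error common to both extremes, and taking extremes picks up noise in the outward direction. A Bland-Altman bias near zero in RoM is therefore compatible with a wrong angle, and a clearly positive one is compatible with an angle that is right on average.

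At stake is what the device analysis can conclude. The prototype is not certified as a medical device, and its use at home is the planned difference between the arms. When the trial result is interpreted, readers will want to know how accurately the device read posture. This paragraph is the article's only stated check of that.

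**Working it through.** The plan gives no figure for agreement, so there is none to reproduce. The check is algebra, followed by illustration with assumed inputs.

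**Model.** Device angle = true angle + c + e(t), where c is a constant offset and e(t) is zero-mean frame noise. RoM is taken as maximum minus minimum, the usual meaning; the article does not define it.

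**Constant offset.** RoM(device) = (max + c) − (min + c) = max − min, so c drops out. For c = 5, 10 and 15 degrees without noise, the RoM difference is 0.0 each time, while the mean frame-by-frame angle error is 5, 10 and 15 degrees.

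**Frame noise.** With c = 0, the expected maximum of a noisy series lies above the true maximum and the expected minimum below the true minimum, so the expected RoM difference is positive. Its size was simulated. Inputs that are assumptions, not in the document: 30 frames/s, one 5 s cosine-shaped repetition, true RoM 80 degrees, 4000 repetitions per setting.

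| Noise SD (degrees) | RoM bias, independent noise | RoM bias, noise autocorrelated at 0.9 | RoM bias, 7-frame moving average | Mean angle error |
|---|---|---|---|---|
| 1 | +2.7 | +1.3 | +0.6 | about 0 |
| 2 | +6.0 | +3.2 | +1.4 | about 0 |
| 3 | +9.5 | +5.5 | +2.3 | about 0 |
| 5 | +17.0 | +10.3 | +4.2 | about 0 |

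Other assumed movements give the same picture. At 5.5 s per repetition and SD 2, unfiltered, the bias is +6.4 degrees for a 60-degree movement and +7.4 for a 20-degree one.

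**What RoM does detect.** A 10% compression of the 80-degree movement gives a difference of 0.9 × 80 − 80 = −8 degrees. Errors can offset each other, however. A 10% compression of the 60-degree movement (−6 degrees) with SD 2 unfiltered noise gives a net RoM bias of about +0.5 degrees.

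**What key-point RMSE adds.** Two-dimensional geometry, with thigh and shank each assumed 0.42 m, flexion 10 to 90 degrees, and the knee key point displaced by a constant 3 cm:

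| Direction of shift | Knee key-point RMSE | Error in flexion angle | Error in RoM |
|---|---|---|---|
| Forward | 3 cm | +5.5 to +8.1 degrees | −2.6 degrees |
| Backward | 3 cm | −6.1 to −8.2 degrees | +2.1 degrees |
| Along the limb | 3 cm | about 0 | +0.2 degrees |

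The RMSE is the same in all three rows. It flags the displacement but does not separate over-reading, under-reading and no angle error. RoM moves, but by much less than the angle.

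**What the direct comparison gives.** Device minus reference on synchronised frames returns c as the bias. The frame-by-frame RMSE is √(c² + SD²); for c = 10 and SD = 2, √104 = 10.2 degrees. The frame must be set by the reference: with SD 2 and no offset, the device's own maximum overshoots the true peak by about 3.0 degrees (half of the +6.0), whereas the device reading at the reference-defined peak is unbiased.

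**The case against.** The strongest reply is that constant error is already covered. The prototype's angles come from its key points, so a persistent angle error needs displaced key points, and the planned RMSE registers those. This stands in part. A reader might infer that the agreement analysis is blind to constant error; it is not. What the RMSE does not give is the angle error's sign or its size in degrees.

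Second, RoM is not uninformative. It detects scale errors, it moves somewhat when a single key point is displaced, and it is the metric of the three primary outcomes. A reader might infer that RoM should be replaced or demoted; that would discard a direct check of scale error.

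Third, the noise figures are assumptions. Frame rate, noise level and prototype smoothing are not given. The repetition time of 5 to 6 seconds in the Group Exercise Program section applies to certain group exercises, whereas the agreement test uses a home-programme set with no stated tempo. This stands: only the direction of the effect is established.

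Fourth, a reader might infer that the analysis could pass a device that coaches patients into a wrong position, or fail a sound one. The article does not support this. It sets no pass or fail rule and does not say which quantity drives the feedback score. If scoring uses excursion, RoM is directly relevant and its noise inflation is genuine disagreement.

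Fifth, the article condenses a fuller protocol, which could contain more agreement measures. But the article does name its angle variable; the point concerns that stated choice.

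**Conclusion.** The point holds in a limited form. As stated, the plan's angle-level agreement rests on RoM alone, and RoM agreement cannot establish that the prototype's trunk-thigh and thigh-shank angles agree with the reference. Together, the two planned measures show whether key points are displaced and whether excursion is scaled, but leave angle bias in degrees unquantified.

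The cancellation of a constant offset is exact under the maximum-minus-minimum reading. The positive bias from zero-mean noise is certain in direction. In the main simulation it ranges from +0.6 degrees (SD 1, smoothed) to +17.0 degrees (SD 5, unfiltered), so no single figure should be attributed to this device.

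The consequence is confined to a supplementary device analysis. A reader might infer that the treatment effect is at risk; it is not, because the primary outcomes are measured with the reference system. This is a worthwhile, nearly free improvement, not a flaw in the trial's main comparison.

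**What to change.** Keep the key-point RMSE and the RoM Bland-Altman plot. Add to the agreement paragraph of Statistical Analysis, in substance:

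- For the trunk-thigh and thigh-shank angles, take device minus reference, in degrees, at the reference-defined peak and minimum frame of each repetition, and report Bland-Altman bias and 95% limits of agreement for each.
- Report the frame-by-frame angle RMSE over the synchronised curves. Signed differences averaged over a whole repetition can cancel, so they should not stand alone.
- Allow for several repetitions per participant with a participant random effect, so that the limits use both between- and within-participant variance: bias ± 1.96 × √(between variance + within variance).
- State how RoM is computed and whether the prototype signal is smoothed beforehand.

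The cost is a few sentences and some extra scripting. The systems are already to be synchronised in time and space and the key-point coordinates stored, so no further measurement or participant burden arises.
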